
### Data Analysis

Descriptive statistics, such as proportions, means, and standard deviations, will be used to summarize the baseline and end-of-study variables across the 3 study groups (groups A, B, and C) and to assess the distributional assumptions of the statistical techniques used. For the primary objective, data on recruitment rate, randomization process, interventions, clinical and ICT outcome measures, dropout rates, and adherence rates for the interventions will be collected. For the secondary objective, a repeated measures analysis of variance with the fixed-factor study group (A, B, or C) and the within-factor assessment time (0, 6, and 12 weeks) will be conducted to compare groups for the clinical outcome measures at 0, 6, and 12 weeks. An intention-to-treat analysis will be conducted and mixed model repeated measures will be considered to accommodate missing data.

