**Objective:**

The primary aims of the proposed pilot randomized controlled trial (RCT) are to examine (1) the feasibility of conducting a full-scale RCT to evaluate the effectiveness of two popular types of PA: a yoga training program and an aerobic dance training program, in female adolescents (aged 13-18 years) with JIA compared with an electronic pamphlet control group; and (2) the acceptability of these interventions.

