**Conclusions:**

To our knowledge, this is the first study to evaluate the effectiveness of yoga and aerobic dance as pain management interventions for female adolescents with JIA. The use of online programs to disseminate these 2 PA interventions may facilitate access to alternative methods of pain management. This study can lead to a full-scale RCT.

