### Objectives

The primary objectives of the proposed single-blind three-arm pilot RCT with a parallel group will be to examine (1) the feasibility of a 12-week full-effectiveness trial of two popular types of PA and an electronic pamphlet control group: group A: an online yoga training program and a PA electronic educational pamphlet; group B: an online aerobic dance training program and a PA electronic educational pamphlet; group C: an electronic pamphlet control group (PA electronic educational pamphlet) postintervention; and (2) the acceptability of the yoga and aerobic dance PA interventions. The secondary objective of this pilot RCT will be to examine the initial effectiveness of a yoga training program (group A) and an aerobic dance training program (group B) on pain intensity, participation in PA, morning stiffness, functional status, self-efficacy, fatigue, patient global assessment, disease activity, and adverse events in female adolescents (aged 13 to 18 years) with JIA compared with an electronic pamphlet control group (group C) postintervention.

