Feasibility will be assessed by the recruitment rate, the randomization process, and self-reported adherence and measured using a questionnaire, as well as protocol deviations, dropout rates, and percentage of missing data in the questionnaires.Recruitment rate: The number of participants recruited in the trial and the time used for recruitment will be documented in a feasibility form. The number of participants will be divided by the duration of recruitment. This will be measured on a continuous basis for up to 12 weeks.Randomization process: The ease at which the randomization process is conducted will be described by researchers in a feasibility form. This will be measured on a continuous basis for up to 12 weeks.Number of protocol deviations: The number of protocol deviations, the time at which they occur, the group in which they occur, and the potential reasons for these will be documented in a feasibility form. Participants will be asked why they deviated from the protocol by researchers using a feasibility form. This will be measured on a continuous basis for up to 12 weeks.Dropout rates: The number of participants who dropped out of the trial, the time at which they dropped out, the group in which they belonged, and the reasons for these will be documented in a feasibility form. Participants will be asked why they dropped out by researchers. The number of dropouts in each group will be divided by the duration of the trial. This will be measured on a continuous basis for up to 12 weeks.Percentage of missing data in the questionnaires: The percentage of missing data in the questionnaires, the time at which they occur, and potential reasons for these will be documented in a feasibility form. This will be measured on a continuous basis for up to 12 weeks.Self-reported adherence: Self-reported adherence to the training programs will be assessed by monitoring the number and length of sessions and dividing the time spent performing the program by the duration of prescribed sessions of either yoga or aerobic dance. Self-reported adherence will be recorded weekly using an adapted online version of the validated 7-day PA Report calendar (in minutes) [62]. This will be measured each week for up to 12 weeks.The acceptability of the yoga or aerobic dance interventions will be assessed using a questionnaire-administered postintervention. Questions will explore the acceptability of online consultations, virtual group sessions, PA videos (either yoga or aerobic dance programs), electronic pamphlet, and training programs (content and duration of the yoga and aerobic dance programs), as well as facilitators and barriers to participating. This questionnaire will be administered at 6 and 12 weeks.The usability of Facebook will be assessed by the System Usability Scale (SUS) [63,64]. The SUS is composed of 10 items using a 5-point scoring system ranging from Strongly Disagree (a score of 1 out of 5 for each question) to Strongly Agree (a score of 5 out of 5 for each question). The total score ranges from 5 (low usability) to 50 (high usability). The usability will be measured at 6 and 12 weeks.The usability of the videoconferencing platform will be assessed by the SUS [63,64]. The SUS is composed of 10 items using a 5-point scoring system ranging from Strongly Disagree (a score of 1 out of 5 for each question) to Strongly Agree (a score of 5 out of 5 for each question). The total score ranges from 5 (low usability) to 50 (high usability). The usability will be measured at 6 and 12 weeks.The use of Facebook will be assessed by the number of posts, live online discussions, and views of the videos. The use will be measured at 6 and 12 weeks.

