### Sample Size Calculation for Future Full-Scale RCT

The current sample size is adequate for pilot studies involving group comparisons to assess feasibility and to estimate the variance to determine the sample size for a definitive trial [76].

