### Conclusions

This pilot RCT has substantial potential to enhance our understanding of the potential effectiveness of popular PA interventions disseminated to patients with JIA using ICTs, making it a novel study. This will help understand which PA intervention has the most potential for improved outcomes. It will also help determine whether these PAs and ICTs are acceptable to youths with JIA and whether a larger trial would be feasible. The proposed pilot RCT will contribute to the knowledge of the effect of a specific functional activity on self-reported pain relief, functional status, and self-efficacy as well as PA adherence, daily pain, and fatigue intensity.

This study could also set the standard for community-based care for female adolescents with JIA. Moreover, other rehabilitation or functional interventions could be examined for youths with other chronic diseases**.**

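### The pilot is meant to inform whether a larger trial is feasible, but no feasibility measure has a prespecified criterion, and dropout as defined is not a proportion

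*Protocol article*

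**What the plan says.** The Abstract's Objective makes it a primary aim to examine "the feasibility of conducting a full-scale RCT to evaluate the effectiveness of two popular types of PA". The Objectives section adds a second primary aim: "the acceptability of the yoga and aerobic dance PA interventions". The Discussion's Conclusions state the use of the results: "It will also help determine whether these PAs and ICTs are acceptable to youths with JIA and whether a larger trial would be feasible". The Abstract's Conclusions add: "This study can lead to a full-scale RCT".

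Outcome Measures goes through the primary measures one by one: recruitment rate, randomisation process, protocol deviations, dropout, missing questionnaire data, self-reported adherence, acceptability, usability of Facebook and of the videoconferencing platform, and use of Facebook. It says how each is recorded or calculated. For recruitment, for instance: "The number of participants will be divided by the duration of recruitment". Dropout is the number of dropouts in each group divided by the duration of the trial. Adherence is time spent on the programme divided by prescribed session time.

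Data Analysis opens with a general plan for descriptive statistics (proportions, means, standard deviations) across the three groups. Its one sentence specific to the primary objective begins "For the primary objective, data on recruitment rate, randomization process, interventions, clinical and ICT outcome measures, dropout rates, and adherence rates for the interventions will" and ends by saying that these data are collected. The secondary objective gets a named model, factors and time points. The sample size section says: "The current sample size is adequate for pilot studies involving group comparisons to assess feasibility". It supports this with a citation and gives no rate, precision or cut-off.

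**The concern.** A pilot whose results feed a decision about a larger trial needs some stated standard against which its rates will be read. Here each measure has a recording rule and none has a criterion. The same team that observes the rates would then also choose the standard, after seeing them. Blinding the data analyst does not help, because overall recruitment, retention and missing data need no group labels.

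The conclusion on the primary objective is at stake. With 25 participants (10, 10 and 5 by group), moderately different standards can turn the same data from encouraging to discouraging, and a standard set afterwards cannot be shown to be independent of the result.

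A second, smaller problem is the dropout formula. A count divided by calendar time has no participant denominator, so it cannot be compared between groups of different size or set against a percentage.

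**Working it through.** **Step 1. Is there a criterion anywhere?** Each measure under Outcome Measures was checked, and then Data Analysis, the sample size section and the Discussion.

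| Measure | What is fixed | Criterion |
|---|---|---|
| Recruitment rate | number recruited / recruitment duration | none |
| Randomisation process | narrative on ease | none |
| Protocol deviations | count, time, group, reasons | none |
| Dropout | count per group / trial duration | none |
| Missing questionnaire data | percentage, time, reasons | none |
| Adherence | time performed / time prescribed | none |
| Acceptability | exploratory questionnaire | none |
| Usability (two platforms) | score range | none |
| Facebook use | counts | none |

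Measures with a stated criterion: 0. The sample size section and the Discussion add none.

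**Step 2. The plan's own figure.** The only number to reproduce is the allocation: 25 × (2/5, 2/5, 1/5) = 10, 10, 5, which agrees. The total of 25 cannot be re-derived, because its stated basis is a citation.

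**Step 3. How much does the choice of mark matter at n = 25?** The article gives no expected rates, so the true rates and marks below are assumptions. With X retained out of 25 and true retention p, X is Binomial(25, p) and the chance of meeting a mark r is P(X ≥ r).

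At p = 0.75:

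| Mark | P(X ≥ r) |
|---|---|
| 15/25 (60%) | 0.970 |
| 18/25 (72%) | 0.727 |
| 20/25 (80%) | 0.378 |
| 23/25 (92%) | 0.032 |

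At other true rates:

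| Mark | p = 0.60 | p = 0.80 |
|---|---|---|
| 15/25 | 0.59 | 0.99 |
| 18/25 | 0.15 | 0.89 |
| 20/25 | 0.03 | 0.62 |
| 22/25 | 0.002 | 0.23 |

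A pass probability always depends on the threshold. The table shows only how much room an unstated threshold leaves in a trial of this size.

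**Step 4. Precision.** Exact (Clopper-Pearson) 95% intervals:

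- 15/25 = 60%: 39% to 79%
- 20/25 = 80%: 59% to 93%
- 16/20 in the two exercise groups = 80%: 56% to 94%
- 8/10 in one exercise group = 80%: 44% to 97%
- 4/5 in the control group = 80%: 28% to 99%

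The intervals for 60% and 80% retention overlap widely. Setting a mark in advance does not change them.

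**Step 5. The dropout formula.** Taking trial duration as 12 weeks:

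- Exercise group, 2 of 10 lost: 2/12 = 0.17 per week; as a proportion, 2/10 = 20%.
- Control group, 2 of 5 lost: 2/12 = 0.17 per week; as a proportion, 2/5 = 40%.

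The defined measure is identical where the proportions differ by a factor of two.

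**Step 6. An example rule.** Retention go at ≥ 20/25, stop at ≤ 15/25, otherwise amend:

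| True retention | P(go) = P(X ≥ 20) | P(stop) = P(X ≤ 15) | P(amend) = 1 − P(go) − P(stop) |
|---|---|---|---|
| 60% | 0.03 | 0.58 | 0.40 |
| 80% | 0.62 | 0.02 | 0.37 |
| 85% | 0.84 | 0.002 | 0.16 |

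Rows may miss 1 by rounding.

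**Step 7. Combining several rules.** Requiring go on every measure is costly. A retention rule that passes 84% of the time and an adherence rule that passes 80% pass together 0.84 × 0.80 ≈ 0.67, if independent. Five measures at 80% each give 0.80⁵ ≈ 0.33. A sound trial would then usually miss an overall go.

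**The case against.** The strongest objection is that this is a condensed article, and progression criteria may stand in a full protocol or analysis plan that is not shown. That possibility stands, and if such criteria exist, one sentence citing them would settle most of the point. It does not dispose of it. The article sets out the primary measures down to their numerators and denominators, has an analysis sentence expressly for the primary objective, and refers to no other document for criteria. The dropout formula is stated in the article and is unsuitable as written.

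Three stronger readings are tempting, and the document does not support them:

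- A reader might infer that the primary question is a strict yes/no verdict. The text speaks of examining feasibility and helping to determine it, which estimation with recorded reasons can partly serve.
- A reader might infer that no analysis of the primary objective is planned, or that any result would be read as feasible. Neither follows. Outcome Measures gives calculations, Data Analysis gives descriptive summaries, and poor recruitment or heavy dropout would still be visible in what is recorded.
- A reader might infer that a prespecified mark would make 25 participants informative enough. It would not: 20/25 is compatible with 59% to 93% with or without a mark.

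It is also fair to say that the marks and true rates used in the working are invented, and that acceptability has no stated score to which a cut-off could be applied.

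**Conclusion.** The point holds in a limited form. The pilot's results are meant to help determine whether a larger trial is feasible. The article provides collection, simple calculations and descriptive summaries, with no prespecified criterion for any measure. Any feasibility conclusion would thus rest on a standard chosen after the rates are known.

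As an illustration of size, at an assumed true retention of 75% the chance of meeting the standard runs from 97% (mark of 15/25) to 3% (mark of 23/25). These figures assume independent participants and marks that the article does not contain. They show the latitude left open; they do not predict how the team would use it.

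Separately, and without any assumed rates, the dropout measure cannot be judged as a proportion: over 12 weeks, 20% loss in an exercise group and 40% loss in the control group both come out at 0.17 per week.

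This should be corrected before recruitment. It does not invalidate the design.

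**What to change.** Before recruitment (the article reports none as of May 11, 2020), amend the following.

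1. **Outcome Measures and Data Analysis.** Replace dropouts over duration with 12-week retention as a proportion of those randomised, overall and by group. Report adherence and questionnaire completeness as proportions too. All get exact 95% confidence intervals. For adherence, state the denominator (4 × 60 × 12 = 2,880 minutes, or 3 × 60 × 12 = 2,160 if only individual sessions count) and the cut that classes a participant as adherent.
2. **Progression criteria.** Prespecify go / amend / stop cut-offs for a few measures already collected, such as retention, and adherence in groups A and B. Example for the team to adjust: retention go at ≥ 20/25, stop at ≤ 15/25, otherwise amend, with the operating characteristics in Step 6. If criteria already exist in another document, cite them.
3. **Status of the criteria.** Use them as guidance for the progression decision. Avoid a rule that takes the worst category across all measures, unless its joint operating characteristics are stated.
4. **Acceptability and ease of randomisation.** Keep these descriptive unless a scored item exists.
5. **Sample size section.** Alongside the adequacy statement, give the precision that 25 participants provide, for example 59% to 93% for 20/25.

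The cost is about a paragraph or a little more of text, with no new participants or data. The downside is that the team is held to marks it could miss: a trial with true retention of 80% would miss the example go mark 38% of the time (1 − 0.62). The estimates remain imprecise in either case.

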### Recruitment

The recruitment of a convenience sample of 25 participants (in a ratio of 2:2:1) will be performed at the Children’s Hospital of Eastern Ontario (CHEO) Pediatric Rheumatology Clinic. Rheumatologists at the CHEO Rheumatology Clinic will be provided with the inclusion and exclusion criteria for the study. During regular scheduled visits, treating rheumatologists will identify and direct eligible participants with JIA (and their parents) to the research coordinator who will explain the study in detail. Eligible participants will be invited to complete a screening questionnaire to ensure that they meet the study selection criteria before central randomization. If eligible, participants will be asked to sign either a consent form if they are able to consent or an assent form and their parent/guardian will be asked to sign a consent form. They will also complete a questionnaire that will gather sociodemographic and medical information as well as a validated questionnaire on participation in PA. They will also be asked about their preference in terms of PA.

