### Participant Allocation

Once informed consent is obtained, participants will be randomly assigned to one of the 3 groups using the central randomization scheme [60] and based on a sequence of computer-generated random numbers using a blocking factor (randomly varying between 6 and 9). The central stratified randomization process will be based on age (between 13 and 15 years and between 16 and 18 years).

Before running the randomization program, the data manager will document the participant’s initials (first and last names) and date of birth (month and year). After running the program, the data manager will prepare sealed opaque envelopes with the group allocation and study ID number for each patient and will provide it to the research coordinator. Participants will open the sealed opaque envelope containing their group assignment and a confidential link to access their Facebook group page where further instructions can be found. The research coordinator will explain the procedures related to the group assigned and will ask participants to indicate their availability for an initial individual online consultation as well as for virtual group sessions. Participants will be asked not to change their usual level of PA during the study except for following the program to which they were assigned.

At the clinic, participants will complete a questionnaire that will gather the following information:

Sociodemographic information: partial date of birth (month/year), age, gender, ability to understand English, and ability to use and access the internet weekly for the study duration.Medical information: diagnosis, partial date of diagnosis (month/year), disease duration, presence of serious chronic diseases (eg, cancer or other illnesses) or cognitive impairments, presence of contraindications to exercise (as determined by the treating rheumatologist), current use of JIA-specific medication, anticipated change in JIA-specific medication in the next 12 weeks, and use of physical interventions/treatments other than the prescribed medication for JIA pain relief and pain level when performing regular activities. A chart review will help verify this information.PA information: the amount of PA performed weekly using a validated exercise log [61] and preferences in terms of PA (eg, yoga, Zumba, or other types).

At baseline, all the participants will be asked to do the following:

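### The repeated measures ANOVA treats week 0 as an outcome, has no baseline or age-stratum term and names no postintervention contrast; the mixed model that intention-to-treat needs is only an option

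*Protocol article*

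**What the plan says.** All references are to the protocol article.

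- **Data Analysis** names the model for the secondary objective as "a repeated measures analysis of variance with the fixed-factor study group (A, B, or C) and the within-factor assessment time", and gives its purpose as "to compare groups for the clinical outcome measures at 0, 6, and 12 weeks". No other model term is mentioned.
- The next sentence of **Data Analysis** reads: "An intention-to-treat analysis will be conducted and mixed model repeated measures will be considered to accommodate missing data".
- **Objectives** sets the target of the secondary objective: yoga (A) and aerobic dance (B), "compared with an electronic pamphlet control group (group C) postintervention".
- **Participant Allocation** states: "The central stratified randomization process will be based on age", with strata 13 to 15 and 16 to 18 years.
- **Recruitment** gives the size and ratio: "The recruitment of a convenience sample of 25 participants (in a ratio of 2:2:1"), which makes 10, 10 and 5.
- **Sample Size Calculation for Future Full-Scale RCT** gives the rationale: "The current sample size is adequate for pilot studies involving group comparisons to assess feasibility and to estimate the variance". It states no effect size, standard deviation, correlation or dropout.
- On patient global assessment the sections disagree. **Participant Allocation** lists it among the baseline questionnaires. **Outcome Measures** schedules it at weeks 6 and 12 only, and **Outcomes** mentions it only postintervention.

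**The concern.** The question asked and the model named do not match. The objective concerns two differences after the intervention. The model compares three groups over three visits, the first of which precedes any training. Its two candidate tests are the group main effect, which averages in week 0, and the group-by-time interaction, which has (3-1)(3-1) = 4 degrees of freedom and isolates neither A-C nor B-C. The baseline value and the age stratum are both collected, but neither is used to reduce residual variance.

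The second problem is missing data. A classical repeated measures ANOVA uses only participants seen at all three visits. That sits badly beside an intention-to-treat commitment, and the method that would resolve it is left as a possibility. The choice could then be made after the pattern of missing data is known. With five controls, the outcome of that choice is visible in the result.

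**Working it through.** **Inputs.** From the document: 25 participants at 2:2:1, so 25 x 2/5 = 10, 10 and 25 x 1/5 = 5, which agrees with the stated arm sizes; visits at 0, 6 and 12 weeks. The plan states no power or precision figure, so there is none to reproduce. Assumed: equal variance at each visit (set to 1), equal correlation r between any two visits (compound symmetry), r from 0.3 to 0.7, and arms equal on average at week 0.

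**1. Group main effect: what it estimates.** Let the week-12 difference be 1.
- Full by week 6: (0 + 1 + 1)/3 = 2/3.
- Building linearly: (0 + 0.5 + 1)/3 = 1/2.

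**2. Group main effect: efficiency.** The variance per participant of the three-visit mean is (1 + 2r)/3. That of the baseline-adjusted week-12 value is 1 - r². Relative efficiency = (fraction recovered)² x (1 - r²) / [(1 + 2r)/3].

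| r | full by week 6 | linear |
|---|---|---|
| 0.3 | 0.76 | 0.43 |
| 0.5 | 0.50 | 0.28 |
| 0.7 | 0.28 | 0.16 |

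At r = 0.5, for example, 0.444 x 0.75/0.667 = 0.50, so the adjusted week-12 contrast carries 2.0 times the information.

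**3. Change from week 0 to week 12.** This is undiluted. Its variance is 2(1 - r), against 1 - r² for the adjusted contrast, a ratio of 2/(1 + r).
- r = 0.3: 2/1.3 = 1.54, or 54% more variance.
- r = 0.5: 2/1.5 = 1.33, or 33% more.
- r = 0.7: 2/1.7 = 1.18, or 18% more.

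For A-C, multiply by 1/10 + 1/5 = 0.3. The 95% half-widths in SD units (t with 22 df for change, 21 df for adjusted) are 1.34 against 1.09 at r = 0.3, 1.14 against 0.99 at r = 0.5, and 0.88 against 0.81 at r = 0.7.

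These figures do not charge the adjusted contrast for chance baseline imbalance when its slope is estimated. With 25 - 3 = 22 within-arm degrees of freedom, that inflates its variance by about 1 + 1/(22 - 2) = 1.05 on average. The ratios become about 1.54/1.05 = 1.47, 1.33/1.05 = 1.27 and 1.18/1.05 = 1.12. The direction holds throughout the range.

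**4. Incomplete records under a classical ANOVA.** One control missing one visit removes 1/5 = 20% of group C. If a fraction m of participants misses any visit (assumed, independent), the expected number of complete controls is 5(1 - m). The chance of three or fewer is 1 - (1 - m)⁵ - 5m(1 - m)⁴.
- m = 10%: 4.5 expected, chance 8%.
- m = 20%: 4.0 expected, chance 26%.
- m = 30%: 3.5 expected, chance 47%.

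**5. Patient global assessment.** On the Outcome Measures schedule there is no week-0 value, so the stated three-visit model cannot be fitted to it. On the Participant Allocation text it can.

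**The case against.** The best defence is that the plan can be read more kindly. Groups are to be compared at each visit, which suggests group-by-time and its contrasts rather than the main effect. Intention-to-treat is promised, and a mixed model is named for missing data. Contrasts and covariates are often left to a statistical analysis plan, which is not shown here. Much of this stands, and it rules out several stronger readings that a reader might infer:

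- *The analysis dilutes the treatment effect.* This is true only if the group main effect is read, and the article does not say which test will be. A week-12 or group-by-time contrast is undiluted.
- *The plan deletes incomplete participants.* It does so only if the classical ANOVA is used despite the following sentence. What the text supports is that the named method and the intention-to-treat commitment conflict and the remedy is optional.
- *Leaving out age distorts the contrast.* It does not. It costs some precision and tends to make standard errors conservative. This is the weakest part of the point and the one most easily covered by an analysis plan.
- *A weakened effect estimate will size the definitive trial.* The article says that the sample serves feasibility and estimation of variance, not of effect.
- *Ignoring the weekly pain and fatigue scores is an error.* Outcome Measures sets these outcomes at baseline, 6 and 12 weeks, and Outcomes describes the weekly collection as monitoring. Modelling the weekly scores, or fitting logistic or ordinal models to categorical items, is optional and fragile with five controls.

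The defence does not reach the model that the article does fix. That model makes baseline a response, and no term or contrast named answers the stated objective.

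**Conclusion.** The point holds in limited form. The model named does not deliver the postintervention A-C and B-C comparisons that the objective asks for, makes no use of baseline or stratum as covariates, and conflicts with intention-to-treat unless the optional mixed model is adopted. The loss depends on which test is read: a third to a half of the effect for the main effect, or 54%, 33% or 18% excess variance for week-12 change at correlation 0.3, 0.5 or 0.7. The correlations, compound symmetry, time course and missingness are all assumed, because the document gives none. The point concerns a secondary objective of a 25-person feasibility pilot and leaves the feasibility aims untouched. It is worth correcting because the remedy is cheap, not because the trial is unsound without it.

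**What to change.** Make the mixed model the stated analysis for the continuous clinical outcomes:

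- responses at weeks 6 and 12;
- fixed effects for arm, week, arm-by-week, baseline value and age stratum (13 to 15, 16 to 18);
- all randomised participants in their assigned arm, so that a participant with only one of the two later visits still contributes;
- A-C and B-C at week 12 reported with 95% confidence intervals and small-sample degrees of freedom.

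Reconcile Participant Allocation with Outcome Measures on whether patient global assessment is taken at baseline. If it is not, fit its model without the baseline covariate.

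The cost is wording, code and two model degrees of freedom (baseline and stratum), which is a real but small charge with 25 participants. No new data are needed, and the article reports that recruitment had not begun.
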